|-----------------------------------------------------------------------------|-----------------------------------------------------------------------------------------------------------------------------------------------------------------------------------------------------------------------------------------------------------------------------------------------------------------------------------------------------------------------------------------------------------------------------------------------------------------------------------------------------------------------------------------------------------------------------------------------------------------------------------------------------------------------------------------------------------------------------------------------------------------------------------------------------------------------------------------------------------------------------------------------------------------------------------------------------------------------------------------------------------------------------------------------------------------------------------------------------------------------------------------------------------------------------------------------------------------------------------------------------------------------------------------------------------------------------------------------------------------------------------------------------------------------------------------------------------------------------------------------------------------------------------------------------------------------------------------------------------------------------------------------------------------------------------|
| 
Administratieve aspecten /
 Administrative aspects
 | 
Alle geïncludeerde voorschool-locaties krijgen een randomisatienummer. / All included preschools will receive a randomisation number. Daarnaast wordt aan alle PMers, kinderen en ouders/verzorgers een deelnemernummer toegekend. Furthermore, a participant number will be assigned to all ECEC teachers, children and parents/caregivers. Vragenlijsten en eet- en beweegdagboeken worden gecodeerd. / Questionnaires and food/physical activity records will be coded. De papieren documenten worden bewaard in een afgesloten ruimte op de HvA, los van de getekende Informed Consent formulieren. / The data on paper will be stored in a locked room at the AUAS, separate from signed Informed Consent forms. Digitale gegevens worden bewaard in mappen op de interne schijf van de HvA. / Digital data will be stored in folders on the internal drive of the AUAS. Alleen onderzoekers van PreSchool@HealthyWeight hebben toegang tot de mappen. / Only the researchers of PreSchool@HealthyWeight will have access to the folders. Digitale gecodeerde gegevens worden tevens opgeslagen via SURFdrive: een veilige persoonlijke cloudopslagdienst voor het Nederlandse onderwijs en onderzoek. / Coded digital data will also be stored on SURFdrive: a secure personal cloud storage service for Dutch education and research. Gecodeerde gegevens die worden opgeslagen op SURFdrive zijn niet herleidbaar tot een individueel persoon. / Coded data on SURFdrive will not be traceable to an individual subject. Alle documenten worden tot 10 jaar na het onderzoek opgeslagen. / All documents will be stored up to 10 years after the end of the study.
 |
|-----------------------------------------------------------------------------|-----------------------------------------------------------------------------------------------------------------------------------------------------------------------------------------------------------------------------------------------------------------------------------------------------------------------------------------------------------------------------------------------------------------------------------------------------------------------------------------------------------------------------------------------------------------------------------------------------------------------------------------------------------------------------------------------------------------------------------------------------------------------------------------------------------------------------------------------------------------------------------------------------------------------------------------------------------------------------------------------------------------------------------------------------------------------------------------------------------------------------------------------------------------------------------------------------------------------------------------------------------------------------------------------------------------------------------------------------------------------------------------------------------------------------------------------------------------------------------------------------------------------------------------------------------------------------------------------------------------------------------------------------------------------------------|

|                                                                                       |                                                                                                                                                                                                                                                                                                                                                                                                                                                                                                                                                                                                                                                                                                                                                                                                                                                                                                                                                                                                                                                                                                                                                                                                                                                                                                                                                                                                                                                                                                                                                                                                                                                                                                                                                                                                                                                                                                                                                                                                                                                                                                                                                                                                                                                                                                                                                                                             |
|---------------------------------------------------------------------------------------|---------------------------------------------------------------------------------------------------------------------------------------------------------------------------------------------------------------------------------------------------------------------------------------------------------------------------------------------------------------------------------------------------------------------------------------------------------------------------------------------------------------------------------------------------------------------------------------------------------------------------------------------------------------------------------------------------------------------------------------------------------------------------------------------------------------------------------------------------------------------------------------------------------------------------------------------------------------------------------------------------------------------------------------------------------------------------------------------------------------------------------------------------------------------------------------------------------------------------------------------------------------------------------------------------------------------------------------------------------------------------------------------------------------------------------------------------------------------------------------------------------------------------------------------------------------------------------------------------------------------------------------------------------------------------------------------------------------------------------------------------------------------------------------------------------------------------------------------------------------------------------------------------------------------------------------------------------------------------------------------------------------------------------------------------------------------------------------------------------------------------------------------------------------------------------------------------------------------------------------------------------------------------------------------------------------------------------------------------------------------------------------------|
| Publicatiebeleid en amendementen /
Publication Policy and Amendments | Publicaties in professionele- en wetenschappelijke tijdschriften worden beoogd. Daarnaast wordt nagestreefd om op lokale, landelijke en internationale podia presentaties te geven. / Publications in professional and scientific journals are intended. In addition, it is aimed to present results on local, national and international conferences.                                                                                                                                                                                                                                                                                                                                                                                                                                                                                                                                                                                                                                                                                                                                                                                                                                                                                                                                                                                                                                                                                                                                                                                                                                                                                                                                                                                                                                                                                                                                                                                                                                                                                                                                                                                                                                                                                                                                                                                                                               |

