|  | 
baseline and close out measurements will be carried out. Na de nulmeting bij PMers, kinderen en hun ouders/verzorgers, starten PMers op een interventielocatie met het programma EGS2. / After baseline measurements, ECEC teachers at intervention preschools will start with the AHS training. De training bestaat uit drie bijeenkomsten en gaat aan de hand van theorie en opdrachten in op een gezonde leefstijl van PMers, kinderen en hun ouders/verzorgers. / The training consists of three meetings and based on theory and assignments, ECEC teachers will learn about pursuing a healthy lifestyle. Bijeenkomst 1 is gericht op een gezonde leefstijl van kinderen en PMers zelf. / Meeting 1 focuses on a healthy lifestyle for children and on the ECEC teachers' personal lifestyle. In bijeenkomst 2 wordt aandacht besteed aan de interactie met kinderen rondom een gezonde leefstijl. / In meeting 2, the interaction with children regarding a healthy lifestyle will be discussed. De laatste bijeenkomst gaat over de interactie met ouders/verzorgers t.a.v. een gezonde leefstijl van hun kind(eren). / The third meeting will concern the interaction with parents/caregivers regarding a healthy lifestyle for their child. De training begint met een instaptoets voor het toetsten van initieel kennisniveau van PMers en wordt afgesloten met een eindtoets. / The training starts with an test to examine the initial knowledge level of ECEC teachers and concludes with a final test. Aansluitend op het programma vindt een periode plaats (<math>\pm</math> 3 maanden) waarin PMers verkregen kennis en vaardigheden t.a.v. een gezonde leefstijl in de praktijk brengen. / After the training, there is a period (<math>\pm</math> 3 months) in which ECEC teachers can put the gained knowledge into practice. PMers krijgen een actieve rol door feedback te geven aan ouders/verzorgers op het voedings- en beweeggedrag van hun kind(eren). / ECEC teachers can have an active role by giving feedback to parents/caregivers on the eating behaviour and physical activity level of their child(ren). Deze feedback is gebaseerd op een uitgebreide analyse van het voedings- en beweeggedrag van de kinderen (gegevens verzameld bij de nulmeting van kinderen en hun ouders/verzorgers) en wordt uitgevoerd door onderzoekers en studenten van de HvA. / The feedback is based on an analyses of the eating and physical activity behaviours of children (data obtained at baseline and close out measurements by researchers and students of the AUAS).
 |

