|  | 
De nul- en nameting voor PMers bestaat uit: / The baseline and close out measurements for ECEC teachers will consist of:
 
 
- Het invullen van een vragenlijst (Gubbels, Sleddens, Raaijmakers, Gies, & Kremers, 2015) gericht op kennis, attitude en vaardigheden t.a.v. een gezonde leefstijl. In de vragenlijst komt het vertrouwen van PMers in het goed kunnen ondersteunen van kinderen en hun ouders/verzorgers bij een gezonde leefstijl aan bod. Tevens worden bij de nulmeting in deze vragenlijst enkele demografische kenmerken nagevraagd. / Questionnaires about knowledge, attitude and practices regarding a healthy lifestyle. In the questionnaires also the level of confidence of ECEC teachers in supporting children and their parents/caregivers in pursuing a healthy lifestyle will be checked. Furthermore, demographic characteristics will be obtained at baseline.
 
- Het meten van lengte en gewicht (voor het berekenen van de BMI). / Height and weight measurements (to calculate BMI).
 
- Het meten van lichaamssamenstelling middels Bio-elektrische Impedantie Analyse (BIA). / Body composition measurements via Bioelectrical Impedance Analysis (BIA).
 
- Het invullen van een 3 daags eetdagboek. / 3-day food records.
 
- Het invullen van een 3 daags beweegdagboek. / 3-day physical activity records.
 
- Het meten van fysieke activiteit op 7 dagen met een Physical Activity Monitor (PAM). / Physical activity measurements via a Physical Activity Monitor (PAM) – 7 days.
 
 
Getrainde studenten van de HvA meten lengte, gewicht en lichaamssamenstelling van een PMer op de voorschool-locatie zelf. / Trained students of the AUAS will measure height, weight and body composition of the ECEC teachers at preschool. Na de metingen wordt op papier een vragenlijst en eet- en beweegdagboek met bijhorende informatie verstrekt. / After the measurements, a questionnaire, food record and physical activity record will be provided on paper. Daarnaast wordt een PAM meegegeven. / Furthermore, a PAM will be given. Na een week haalt een student de vragenlijst, de PAM, het eetdagboek en het beweegdagboek op bij de voorschool-locatie. / After a week, a student will pick up the questionnaire, PAM, food record and physical activity record at preschool. Hierbij controleert de student de ingevulde vragenlijsten op volledigheid. / The student will check if a questionnaire is completed.
 |

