**Trained students of the AUAS will measure height, weight and body**

**composition of the ECEC teachers at preschool.** Na de metingen wordt

op papier een vragenlijst met bijhorende informatie verstrekt. / **After the measurements, a questionnaire will be provided on paper.** Na een week

haalt een student de vragenlijst op bij de voorschool-locatie. / **After a week, a student will pick up the questionnaires at preschool.** Hierbij

controleert de student de ingevulde vragenlijsten op volledigheid. / **The student will check if a questionnaire is completed.**

De nul- en nameting voor kinderen bestaat uit: / **The baseline and close out measurements for children will consist of:**

- Het meten van lengte en gewicht (voor het berekenen van de BMI). / **Height and weight measurements (to calculate BMI).**
- Het meten van lichaamssamenstelling middels BIA. / **Body composition measurements via Bioelectrical Impedance Analysis (BIA).**
- Een observatie van beweeggedrag (Schulz, Henderson, Sugden, & Barnett, 2011; McKenzie, Marshall, Sallis, & Conway, 2000). / **Observations of physical activity.**

De metingen en observaties vinden plaats op de voorschool-locatie zelf en worden uitgevoerd door getrainde studenten van de HvA. / **The measurements and observations will take place at preschools and will be carried out by trained students of the AUAS.**

De nul- en nameting voor ouders/verzorgers bestaat uit: / **The baseline and close out measurements for parents/caregivers will consist of:**

- Het invullen van een 3 daags eetdagboek van de kinderen. / **3-day food records for their child.**
- Het invullen van een 3 daags beweegdagboek van de kinderen. / **3-day physical activity records for their child.**

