- Een voedselfrequentievragenlijst (Dutman *et al.*, 2011) van de kinderen (de vragenlijst wordt mondeling afgenomen door studenten van de HvA). Naast het eetdagboek (gericht op dag tot dag variatie in voedingsinname), geeft de gevalideerde voedselfrequentievragenlijst aanvullende informatie over voedingspatronen van de kinderen. De verkregen informatie wordt gebruikt door onderzoekers en studenten van de HvA voor het opstellen van feedback aan ouders/verzorgers. De voedselfrequentievragenlijst wordt alleen bij de nulmeting afgenomen. / **Food Frequency Questionnaires for their child (the questionnaire will be administered orally by AUAS students). In addition to the food record (focusing on day-to-day variation in food intake), the validated Food Frequency Questionnaires provides additional information about the children's dietary patterns. The obtained information will be used by researchers and students of the AUAS to prepare feedback for parents/caregivers. The Food Frequency Questionnaires will only be carried out at baseline measurements.**
- Een vragenlijst (Musher-Eizenman, Holub, 2007; O'Connor *et al.*, 2014) gericht op kennis, attitude, vaardigheden en ouderbetrokkenheid t.a.v. een gezonde leefstijl van het kind. Daarnaast worden bij de nulmeting in deze vragenlijst enkele demografische kenmerken nagevraagd (de vragenlijst wordt mondeling afgenomen door studenten van de HvA). / **Questionnaires about knowledge, attitude and practices regarding a healthy lifestyle. At baseline, also demographic characteristics will be obtained (the questionnaire will be administered orally by AUAS students).**

Bij kinderopvangorganisatie Impuls bestaat de afspraak dat ouders/verzorgers minimaal 15 minuten aanwezig zijn op de voorschool.

/ **At the preschools of child care organisation Impuls, it is agreed that parents/caregivers are present at the preschool for at least 15 minutes.**

Deze tijd kan gebruikt worden voor het afnemen van de vragenlijsten. / **This time can be used to administer the questionnaires.** Tevens wordt op papier het eet- en beweegdagboek met bijhorende informatie verstrekt. /

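### AUAS students help prepare the feedback given only to intervention families and also observe children and interview parents at close-out, with no separation of tasks or assessor masking stated

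*Protocol*

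**What the plan says.** All of this stands in the protocol, mostly under Interventie / Intervention.

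- **Preparing feedback.** On the food frequency information collected from parents: "The obtained information will be used by researchers and students of the AUAS to prepare feedback for parents/caregivers". The Dutch text on the diet and activity analysis behind the feedback says that it "wordt uitgevoerd door onderzoekers en studenten van de HvA" (HvA is the Dutch abbreviation for AUAS), that is, carried out by the researchers and students. Teachers then give the feedback to parents.
- **Who receives it.** Intervention families do (section on advantages of participating). Control families do not (end of the intervention description).
- **Assessing children.** "The measurements and observations will take place at preschools and will be carried out by trained students of the AUAS". The list of assessments at baseline and close-out includes "Observations of physical activity".
- **Interviewing parents.** For the questionnaire on knowledge, attitude, practices and engagement: "At baseline, also demographic characteristics will be obtained (the questionnaire will be administered orally by AUAS students".
- **Measuring teachers.** "Trained students of the AUAS will measure height, weight and body composition of the ECEC teachers at preschool". Their questionnaire, which contains the confidence item, is handed out on paper and collected a week later.
- **Allocation** is by preschool (Study design).
- **Coding.** Administrative aspects provides randomisation numbers for preschools, participant numbers, and coded questionnaires and records.

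**The concern.** Students of one institution contribute to a component of the intervention and also collect outcomes, and the protocol puts no barrier between the two tasks. Because whole preschools are allocated, a student who prepared feedback for one family knows the arm of every family at that site. If that student returns at close-out to watch the children or question the parents, the assessment is not masked.

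The methods matter here. In a face-to-face interview about healthy-lifestyle practices, the way a question is put or an answer recorded can be affected by what the interviewer expects. Observation of activity rests on the observer's judgement. An assessor who knows the arm can shift such outcomes towards the intervention when nothing has changed. Randomisation does not protect against this, because the shift arises after allocation and differs by arm. The trial's conclusions about parents and about children's activity and motor development would be at stake.

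This is not a detail that a statistical analysis plan would settle. Who collects the outcomes, and what they know, is study conduct, and no analysis can restore masking after close-out.

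**Working it through.** **Step 1: the two tasks side by side**

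| | Preparing feedback | Assessing at close-out |
|---|---|---|
| Who | AUAS researchers and students | AUAS trained students (children); AUAS students (parent interview) |
| Arms | Feedback reaches intervention families only | Both arms |
| Where | Not stated | At the preschool (children) |
| Separation or masking stated | None | None |

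The coding under Administrative aspects protects identity in the data. It does not keep an assessor standing in the preschool from knowing its arm.

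**Step 2: is the parent interview also oral at close-out?** The English sentence places the oral mode next to the baseline demographics, but the parenthesis concerns the questionnaire as a whole, and the questionnaire is listed for both baseline and close-out. The Dutch text under Burden for subjects has parents answering questions twice, whereas it has teachers filling in a form. Oral administration at close-out is the natural reading.

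**Step 3: which outcomes are exposed?**

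- *Exposed:* the parent questionnaire scores and the child activity observation. Motor development is a listed child parameter, and the only listed assessment it appears to come from is that observation, so it is counted here.
- *Little exposed:* height, weight and body composition, which are instrument readings.
- *Not exposed by this route:* teacher confidence (paper, self-completed) and the children's food and activity records (paper, completed by parents). The food frequency questionnaire is oral, but "The Food Frequency Questionnaires will only be carried out at baseline measurements".

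**Step 4: how much could a modest shift matter?** The protocol gives no size for assessor influence, so a shift *b* of 0.1 or 0.2 SD is assumed. Precision comes from the Sample size section: 120 children per group, two-sided 5%, 80% power, detectable d of 0.35 to 0.40.

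That range reproduces. Detectable d = (1.960 + 0.842) × √(2/n), which is 0.362 for n = 120 and 0.381 for n = 108 (120 less the 10% drop-out assumed for teachers).

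Implied standard error in SD units: SE = d / 2.802.

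- d = 0.40: SE = 0.40 / 2.802 = 0.143
- d = 0.35: SE = 0.35 / 2.802 = 0.125

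With no true effect and a net shift *b*, the rejection rate is P(Z > 1.96 − b/SE) + P(Z < −1.96 − b/SE).

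| Assumed shift | d = 0.40: b/SE | Rejection rate | d = 0.35: b/SE | Rejection rate |
|---|---|---|---|---|
| 0 | 0 | 5% | 0 | 5% |
| 0.1 SD | 0.70 | P(Z > 1.26) + P(Z < −2.66) = 10.8% | 0.80 | P(Z > 1.16) + P(Z < −2.76) = about 13% |
| 0.2 SD | 1.40 | P(Z > 0.56) + P(Z < −3.36) = 28.8% | 1.60 | P(Z > 0.36) + P(Z < −3.56) = about 36% |

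A separate calculation from the group size gives similar figures. With 108 per arm the rates are 11% and 31%. With an assumed design effect of 1.25 they are 10% and 26%.

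**The case against.** The strongest reply is that the text names an institution, not individuals. A reader might infer that one student writes a family's feedback and later interviews that family, or that close-out assessors will know the arm. The protocol says neither. It gives measurement of children to trained students, and feedback to researchers and students, without saying that one roster does both. Teachers, not students, deliver the feedback, so the picture of an interviewer prompting a parent on the interviewer's own advice is further from the text than it first seems. This stands, and it limits the point to what assessors can know.

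A reader might also infer that students help run the teacher training or PLAYgrounds. No passage gives them that role; PLAYgrounds is taught by a trainer.

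It can also be said that separating the tasks would not achieve full masking. Close-out of the children is on site, the playground may look different, and teachers and parents know their arm. Parents' own knowledge of allocation affects their answers whoever asks the questions. This stands too. It argues for declaring the limit, but it is no reason to leave an avoidable route open.

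Finally, the shift of 0.1 to 0.2 SD has no source in the protocol, and the calculation supposes that assessors err on balance in the same direction. That is correct, so the rates illustrate sensitivity and do not predict bias.

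**Conclusion.** The point holds in a limited form. As written, the protocol allows people who know a preschool's arm to collect rater-dependent outcomes at close-out, and it states neither a separation of tasks nor masking. Two groups of secondary outcomes are exposed: the parent questionnaire scores, and children's observed activity and motor development.

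The size is conditional. Under an assumed net shift of 0.1 or 0.2 SD and no true effect, a nominal 5% error rate becomes about 11% or 29% at the precision implied by d = 0.40, and about 13% or 36% at d = 0.35. Applying this to the parent scores also assumes that the precision stated for the children carries over to parents, who are planned in matching numbers.

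A reader might conclude that the trial's main result is compromised. The protocol does not support that: the primary endpoint is self-completed on paper and is not reached by this mechanism. It is self-reported by teachers who know their arm, but that is a different matter, which assessor masking would not remove. The point is a worthwhile, inexpensive improvement to conduct and does not make the design invalid.

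**What to change.** Add to the intervention and measurement description:

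1. A student who analysed data or prepared feedback for a preschool does not observe children or interview parents at that preschool at close-out. The existing students are assigned by preschool to respect this.
2. Assessing students are not told the preschool's allocation.
3. Masking may still fail, because children are assessed on site, a playground may have visibly changed, and teachers and parents know their arm. The parent questionnaire and the observed child outcomes are reported with that limit.

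This adds no participants, visits or burden. It requires planning the rota within the existing student pool, and the price is less flexible scheduling. The protocol gives no student numbers, so the sponsor should confirm that there are enough students to swap between preschools.
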